#### Statistical analyses

Training effects will be tested by evaluating differences between the measurement times using linear and general mixed models. Baseline values of the first measurement time point will be considered as covariates. Clinics are modeled as fixed effect. Key demographic variables such as age, gender and occupation will be used to calculate selectivity in dropout rates. Missing data per measurement point, but also over time, will be treated by advanced methods to handle missing data such as the full information maximum likelihood method (FIML; this will be the same in all other phases, too).

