### Phase 2: quasi-experimental efficacy study

#### Aim/overview of research questions and methods

In Phase 2 (see Fig. 2 and Fig. 5 in Appendix), the effectiveness of the communication competences intervention for the target group of patients and their social support providers will be tested using the gold standard, i.e. a randomized control trial (RCT). This intervention will be based on all stages of Phase 1 of this project, and thus will be developed in a participatory approach with patients and professionals working in the clinics [63]. The intervention will enable patients and social support providers to gain knowledge about the prevalence of pAEs and communication problems as well as expectations of action results. Moreover, it will allow participants to practice communication competences and develop their self-efficacy. Furthermore, the intervention will utilize the provided theoretical input in order to integrate theory into everyday hospital life by means of action and coping plans. To implement the acquired competences as effectively as possible, the following three components will be addressed in the intervention [65]:
the motivation or intention to communicate effectively and confidently with each other,the knowledge of what is crucial for effective communication,the ability to communicate effectively.

The intervention is based on the HAPA model as a social-cognitive model for behavioral change [25] and communication competences (see description of the training above in Phase 1). Participants will be trained in groups by specialized instructors over the course of one and a half days in facilities of the participating clinics (see Table 5, and  Fig. 5 in Appendix).

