#### Procedure

In each hospital, four *professionals will be taught in a train-the-trainer seminar* to train patients and their social support providers based on the short manual developed to teach communication competences. Recruitment will take place via the doctors, nurses and midwives in the hospitals (Fig. 5 in Appendix). The quality management departments will be involved to ensure adequate enrollment in order to reach the target sample size of N = 423 participants. Informed consent will be collected by on-site project managers. When an expectant mother is admitted to the clinic and agrees to participate in the study, she will be randomly assigned to a training group (IG) or a control group (CG). If she is accompanied by a partner, relative, or close friend, they will be assigned to the same group. All patients and social support providers randomly assigned to the intervention group will receive the same training content over the course of this study. In contrast, the control group will receive the hospital care-as-usual (see Fig. 5 in Appendix).

*Randomization* will be done per site and day (block randomization). The central project coordinator will generate the allocation sequence. Depending on this sequence, all patients admitted to the hospital on that day will be allocated to either the IG or to the CG. Patients and staff will not be informed beforehand on which days allocation to the IG or the CG takes place to prevent biases. Instead, the on-site project manager at each hospital will receive a sealed envelope each day containing this information, enabling them to inform other staff involved as well as enroll and assign participants to the CG or IG treatment. This process allows trial participants, general care providers, outcome assessors and data analysts to remain blinded throughout the allocation sequence. Trial participants and general care providers will be unblinded in case they ask for more information about the training. Revealing a participant’s allocated intervention during the trial can be performed after completion of the IG treatment to disclose the content of the intervention. A flyer will be provided containing this information, which will be also used after the study to disseminate findings and tools. Inclusion and exclusion criteria are outlined in Table 6.

**Table 6 Tab6:** Summary of the inclusion and exclusion criteria

*Inclusion criteria*	*Exclusion criteria*

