Expectant mother or *patient* in gynecology and obstetrics or *social support providers* (spouse/partner, relative, close friend) to be recipient of the training *Professional* in a gynecology and obstetrics hospital to be trainer of the patients and the social support providers	Not proficient in the German language and/or does not have the capability of writing Severe cognitive deficits (unable to read/write/answer questions) and impairments due to diagnosed brain injuries, neurological disorders, etc. Insufficient corrected eyesight (patients must be able to read on the cell phone) Participation in another research study or intervention trial conducted in the clinic
Aged 18 years and above	Younger than 18 years
Healthy volunteers	High risk, emergency case
Declaration of consent for participation in the study	Withdraw of consent for participation in the study at any point in time

According to a power analysis, a sample of *N* = 352 is necessary (alpha error = 0.05, power = 80%, to be analyzed IG _analysis_: *N* = 176; CG _analysis_: *N* = 176) in order to detect an effect size of *d* = 0.3. With an assumed drop-out rate of 20%, *N* = 423 participants (IG _recruited_: *N* = 212; CG _recruited_: *N* = 211) have to be recruited in the study. The pAEs will be collected on an individual basis (anonymized) and coded according to the communication competences (see Fig. 5 in Appendix).

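### Phase 2 allocates whole site-days to one arm, but its 80% power is calculated for independently randomised individuals, and the model as described names no site-day term

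*Protocol article*

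**What the plan says.** The Procedure section of Phase 2 says that randomisation "will be done per site and day (block randomization"), and then: "Depending on this sequence, all patients admitted to the hospital on that day will be allocated to either the IG or to the CG". A sealed envelope goes to each hospital's on-site project manager every day with that day's allocation. The same section also says of each mother that "she will be randomly assigned to a training group (IG) or a control group (CG"), which on its own reads as individual randomisation. On companions: "If she is accompanied by a partner, relative, or close friend, they will be assigned to the same group".

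The sample size below Table 6 states that "a sample of *N* = 352 is necessary (alpha error = 0.05, power = 80"%), with 176 analysed per arm to detect d = 0.3. It mentions no cluster size, ICC or design effect.

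The Phase 2 statistical section plans linear and general mixed models as in Phase 1, an analysis of dyadic data, and adjusted ANCOVAs. The Phase 1 section that it refers back to takes baseline values as covariates and says "Clinics are modeled as fixed effect". No random effects are listed in either section.

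**The concern.** The unit that receives the random assignment is the hospital-day, not the person. People admitted to one hospital on one day may share staff and workload, and a mother and her companion are likely to answer alike. Outcomes within a unit may then be correlated, and 352 people carry less information than 352 independent observations.

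Two things are at stake. The first is certain from the text: the stated power was worked out for a design other than the one described. The second is conditional: if the fitted model has no term for the randomised unit, the standard error of the arm effect is understated. Clinic as a fixed effect removes the difference between the two hospitals, but not day-to-day variation within a hospital. A term for the pair alone would not remove it either.

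Phase 2 is the project's only randomised comparison, and its figure of 176 per group is reused for Phase 3.

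**Working it through.** **Inputs from the article.** d = 0.3, alpha 0.05, power 80%, 176 analysed per arm (sample size paragraph below Table 6); allocation by site and day (Procedure). Sidedness is not stated.

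**Reproducing 352.** The normal approximation is n = 2(1.960 + 0.842)²/0.3² = 174.4, so 175 per arm. The two-sided t-test (noncentral t) gives power 0.799 at 175 and 0.801 at 176 per arm, so 176 per arm and 352 in total, as stated. A one-sided test would need 138 per arm and does not reproduce it. The match leaves no room for clustering: the implied design effect is 1.

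**Putting the design effect in.** The number of participants per site-day (m) and the ICC are not in the article, so both are assumed here and shown as a range.

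- Design effect: DE = 1 + (m − 1) × ICC
- Effective N = 352/DE
- Power = Φ(0.3 × √(176/(2·DE)) − 1.960)
- N that restores the planned power = 2 × 176 × DE, rounded up per arm
- Type I error if site-day is omitted from the model = 2 × (1 − Φ(1.960/√DE))

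Example, m = 4 and ICC 0.05: DE = 1 + 3 × 0.05 = 1.15; effective N = 352/1.15 = 306; 0.3 × √(176/2.30) = 2.624; Φ(2.624 − 1.960) = 0.747.

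| m | ICC | DE | Effective N | Power at 352 | N needed | Type I error if site-day omitted |
|---|---|---|---|---|---|---|
| 2 | 0.01 | 1.01 | 349 | 80.0% | 356 | 5.1% |
| 2 | 0.05 | 1.05 | 335 | 78.4% | 370 | 5.6% |
| 2 | 0.10 | 1.10 | 320 | 76.5% | 388 | 6.2% |
| 4 | 0.01 | 1.03 | 342 | 79.2% | 364 | 5.3% |
| 4 | 0.05 | 1.15 | 306 | 74.7% | 406 | 6.8% |
| 4 | 0.10 | 1.30 | 271 | 69.4% | 458 | 8.6% |
| 8 | 0.01 | 1.07 | 329 | 77.7% | 378 | 5.8% |
| 8 | 0.05 | 1.35 | 261 | 67.8% | 476 | 9.2% |
| 8 | 0.10 | 1.70 | 207 | 57.9% | 600 | 13.3% |

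With the t-test in place of the normal approximation, power is 0.2 to 0.4 points lower (74.4% at m = 4 and ICC 0.05). The correct interval would be √DE times as wide as one that ignores site-day: √1.01 = 1.005 at one end, √1.70 = 1.304 at the other.

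**Pairs.** The abstract counts patients and companions together in the Phase 2 total. If everyone were in a pair, with an assumed within-pair correlation of 0.2 to 0.5 and no day effect, DE would be 1.2 to 1.5 and power 72.9% to 63.2%.

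**Baseline adjustment.** Adjusting for the T1 score multiplies the variance by about 1 − r², where r is the correlation between T1 and T2. It cancels the design effect when r = √(1 − 1/DE): 0.36 for DE = 1.15, 0.51 for 1.35 and 0.64 for 1.70. The article gives no r.

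**The case against.** A reader might infer that the planned analysis treats participants as individually randomised, so that its intervals are too narrow. The article does not support that. It plans mixed models and a dyadic analysis without listing random effects, a detail that an article may leave to the full protocol or analysis plan. Clinic as a fixed effect is reasonable with two clinics and does not exclude a site-day term. The Type I error column therefore applies only if site-day is in fact omitted. What stands is that the article names one grouping term, which is not the randomised unit, and describes the ANCOVAs with no cluster term.

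A reader might also infer that the trial cannot have 80% power. That is not established. Baseline adjustment is planned and could offset some or all of the loss. Enrolment per site-day, after exclusions such as high-risk and emergency cases, may be small, and at m = 2 with ICC 0.01 the loss is negligible. But the stated calculation invokes neither argument, and nothing in the article shows that the favourable end applies.

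Nor does the article say that patients admitted on the same day share a training group. It says only "Participants will be trained in groups by specialized instructors", and a group could pool several days.

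**Conclusion.** The mismatch between the unit of allocation and the power calculation is established from the article alone: whole site-days are allocated, and 352 is the size for independent individuals. The stated 80% is therefore not a figure for this design.

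The size of the shortfall cannot be fixed from the article. Over the assumed range it runs from nil to about 22 percentage points (80% to 58%), before any gain from baseline adjustment. These figures take a common cluster size and a single ICC within the day; unequal days or a higher within-pair correlation would lower power further.

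Any effect on Type I error and interval width remains conditional on site-day being left out of the model.

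**What to change.** 1. Describe Phase 2 as cluster-randomised by site-day, and reconcile this with the sentence that reads as individual assignment.
2. Name the model: outcome at T2 on arm, T1 score and clinic, with a random intercept for site-day and pair nested within it, and small-sample degrees of freedom (Satterthwaite or Kenward-Roger). Cluster-robust errors by site-day are an alternative. Apply the same to the ANCOVAs.
3. Record the allocation day for each participant. The envelope procedure fixes it, but the article does not say that it enters the analysis data. If training groups pool several days, record the group too: a site-day intercept would not capture that clustering, which exists only in the intervention arm.
4. Restate the power at 352 with 1 + (m − 1) × ICC, giving the assumed m and ICC and, if used, the assumed baseline correlation.

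The cost is one extra variable, added model terms and a rewritten power paragraph. The restated power may be noticeably below 80%; if the sponsor wants 80% kept without relying on baseline adjustment, the working shows totals of 356 to 600 analysed over the assumed range.

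### Phase 2 allocation is not concealed within a day: the role that takes consent also holds the envelope fixing the arm for that day's admissions, and the blinding statement cannot hold for participants and care providers

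*Protocol article*

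**What the plan says.** All of the procedure is in the Phase 2 Procedure section of the protocol article.

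- **Unit of allocation.** Randomization "will be done per site and day (block randomization"), and "all patients admitted to the hospital on that day will be allocated to either the IG or to the CG". One allocation therefore covers a whole site-day.
- **Sequence.** "The central project coordinator will generate the allocation sequence".
- **Who learns the arm.** The project manager based at each hospital gets a sealed envelope every day. The article describes its use as "enabling them to inform other staff involved as well as enroll and assign participants to the CG or IG treatment".
- **Who takes consent.** "Informed consent will be collected by on-site project managers". This is the same role.
- **Who recruits.** "Recruitment will take place via the doctors, nurses and midwives in the hospitals".
- **Order for one woman.** She is admitted, agrees to take part, and is then randomly assigned. A companion joins her group.
- **Safeguard.** Patients and staff are not told in advance which days belong to which arm.
- **Blinding.** "This process allows trial participants, general care providers, outcome assessors and data analysts to remain blinded throughout the allocation sequence". Participants and care providers may be unblinded if they ask about the training, and allocation may be revealed after the intervention is completed.

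Elsewhere in the article, the patient training is put at about 8 hours (Phase 1, development of the training), and controls receive usual care. Table 2 measures communication competences with a self-developed questionnaire.

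**The concern.** Concealment requires that whoever decides to approach, screen and enrol a woman cannot know her arm until she is in the trial. Here one role combines consent, knowledge of the arm and assignment, and the arm is shared by all of a site's admissions that day. Knowing the arm could affect whom the manager approaches, how the study is presented, and how the high-risk or emergency exclusion in Table 6 is applied. Randomised days could then yield groups that differ before any training.

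The article calls Phase 2 the gold standard, and Phase 3 reuses its two arms as historical controls, so a selection bias would carry into the app evaluation. The blinding sentence adds to the problem. Read at face value, it tells the reader that a self-reported outcome is protected from expectation effects when it is not.

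**Working it through.** **Step 1. When is the envelope opened?** The article does not say, so both readings need checking.

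- *Reading A: opened before the day's enrolment.* This fits the wording that its content enables the manager to enrol and assign. Every woman that day is then consented by someone who knows her arm.
- *Reading B: sealed until the first woman agrees.* This fits the sentence that puts agreement before assignment. The first woman is concealed; each later one is not. If m women are approached on a site-day, the unconcealed share is (m − 1)/m once the first has agreed: 1/2 for m = 2, 2/3 for m = 3, 4/5 for m = 5. The article does not give m; these values are assumptions. Only a day with a single woman is fully concealed.

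Agreeing first and being assigned second conceals an allocation drawn for that person. It cannot conceal an allocation shared by everyone admitted that day.

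**Step 2. Does the safeguard help?** Not announcing days in advance keeps tomorrow's arm unknown. It does nothing for today's arm once the envelope is open.

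**Step 3. What could an imbalance do?** The planned size comes first. The inputs, from the Phase 2 Procedure section, are d = 0.3, alpha 0.05 and power 80%.

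- Normal approximation: n per arm = 2 × (1.960 + 0.842)² / 0.3² = 174.4, so 175.
- Two-sided t-test: 175.4, so 176 per arm and 352 in total. The plan's figure is reproduced.

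Now suppose selective enrolment leaves a difference of b SD on the outcome with no true effect. With 176 per arm, SE = √(2/176) = 0.1066 SD. The unadjusted two-sided type I error is Φ(b/SE − 1.96) + Φ(−b/SE − 1.96).

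| Assumed b (SD) | b as share of d = 0.3 | b/SE | Type I error |
|---|---|---|---|
| 0.05 | 1/6 | 0.47 | 7.6% |
| 0.10 | 1/3 | 0.94 | 15.5% |
| 0.20 | 2/3 | 1.88 | 46.7% |

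The documents give no value for b. The calculation is unadjusted and treats participants as independent. A larger sample shrinks SE but not b, so it does not help.

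**Step 4. Blinding, role by role.**

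| Role | Can the statement hold? |
|---|---|
| Participants | Only as ignorance of future days. Attending about 8 hours of training, or receiving usual care with no comparison training described, shows what was received. |
| Care providers | Not as a general statement. Other involved staff are told the day's arm, and four professionals per hospital are trained to teach the intervention. |
| Outcome assessors | Not for communication competence where the participant completes the questionnaire. Possible for coding of pAEs. |
| Data analysts | Possible by removing group labels. The envelope does not do this. |

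**The case against.** The strongest reply is that the only explicit order in the text is agreement and then assignment, and that patients are not told their arm beforehand. That stands for the individual woman. A reader might infer that the envelope is always opened before the first consent, or that women consent knowing their arm; the article says neither. The reply does not restore concealment for women who come after the opening.

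Further limits also stand:

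- A reader might infer that the recruiting doctors, nurses and midwives are told the arm. The text says only that other involved staff are informed, which could mean the trainers. The point rests on the project manager alone.
- A reader might suppose that controls are asked for nothing, so that consent must differ sharply by day. Table 2 schedules T1 and T2 for Phase 2 without exempting controls.
- pAEs should not be treated as simply staff-recorded and thus open to expectation bias throughout. Table 2 operationalises them by triggers that include readmissions and length of stay, and the Phase 2 text describes anonymised data that are then coded.
- The blinding sentence is qualified by a reference to the allocation sequence and is followed by provisions for unblinding. Read narrowly, it means only that future days are unknown. That is defensible, but it is not blinding of participants or care providers in the usual sense.
- Baseline values are planned as covariates (Phase 1 Statistical analyses, carried to Phase 2 by reference), with ANCOVAs on factors such as education, anxiety and immigration status. These reduce bias from measured differences, but not from unmeasured ones such as a manager's impression of who would do well, and less reliably if T1 is answered with the arm known.

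**Conclusion.** The concern holds in this form: within a site-day, allocation is not concealed from the person taking consent once the envelope is open, under either reading of the opening time. The blinding statement fails for participants and cannot stand as a general statement for care providers. It does not follow that blinding is impossible for everyone: analysts and pAE coders can be blinded, though by a step other than the envelope.

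The size of any resulting bias cannot be derived from the documents. An imbalance of 0.1 SD, one third of the planned effect, would raise the unadjusted type I error from 5% to about 15.5%. That is an illustration resting on an assumed value, and covariate adjustment would lower it for measured differences. Because selection at enrolment cannot be undone afterwards, this should be settled before Phase 2 recruitment starts.

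**What to change.** 1. Keep the day's envelope sealed, or held by the central coordinator, until the list of that day's consented women and companions with completed T1 is closed. Reveal the arm only then, and add no one to a closed list. Alternatively, have consent and T1 carried out by an existing role that does not know the day's arm.
2. State the time of opening relative to consent and T1 in the Procedure section.
3. Replace the blinding sentence with one saying that participants and care providers are not blinded, and that pAE coders and analysts work without group labels.

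The first change mainly alters the order of steps within existing roles. Its cost is that the arm is disclosed only after the day's list is closed, so arranging the training starts later. The article does not show how easily this fits the admission routine, which the sites should check. If it does not fit, the alternative in item 1 avoids the wait.

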#### Procedure, sample, and data collection

*Training for professionals at the clinics* will integrate the communication competences and will be designed based on the HAPA model. A *short manual* will be provided to support the participants in implementing the lessons they learn into their working practice. Written documentation of the training will also be provided to avoid failure of implementation. The training will be offered to all professionals at both intervention sites. Its effectiveness will be tested in the pre-experimental study, which aims to investigate the association between training participation and the reduction/occurrence of pAEs, to observe the mechanisms that make the training successful with regard to supporting professionals in their work and understanding how patient training can be implemented in Phase 2.

The study (Stage E of Phase 1) has a one-group, pre−/post-design (see Fig. 4 in Appendix). It includes all professionals (e.g., doctors, nursing staff, midwives/obstetricians, training assistants, psychologists) at all locations and intends to recruit a total of *N* = 140 participants without any participant exclusion criteria. Professionals will be trained in interdisciplinary groups of 10 to 12 participants. Recruitment will take place via the hospitals involving line managers, works councils, quality management departments, and HR departments. They will be involved to ensure adequate participant enrollment to reach target sample size. Participants will be included in the analysis only if they provide informed consent, which will be collected by project managers working at the hospitals. Data will be analyzed according to intention to treat. If study participants withdraw their consent to be contacted for follow-up measurements at any point, their contact details will be removed from the database. If they indicate that they do not want their data included in the analyses, their data will also be removed. Otherwise, they will be considered as study dropout. All target criteria are shown in Table 2.

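### Phase 2 allows training content to reach control participants on request or by flyer, with a time limit that is undefined and not tied to their T2 measurement

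*Protocol article*

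**What the plan says.** All the relevant rules are in the Phase 2 Procedure section of the protocol article, in the paragraph on randomisation.

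- **Request rule.** "Trial participants and general care providers will be unblinded in case they ask for more information about the training". It covers participants in both arms and gives no point in time.
- **Disclosure rule.** "Revealing a participant’s allocated intervention during the trial can be performed after completion of the IG treatment to disclose the content of the intervention". The stated purpose is to disclose content, and the only limit is the end of intervention-group (IG) treatment.
- **Flyer.** "A flyer will be provided containing this information, which will be also used after the study to disseminate findings and tools". The word also implies that the flyer is used before the study ends.
- **Control condition.** In the same section, "the control group will receive the hospital care-as-usual".

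Allocation is by site and day, so both arms are recruited and cared for in the same two clinics. Table 2 sets a T1 and a T2 for Phase 2 and gives a self-developed questionnaire as the measure of communication competences. The Phase 2 overview lists three components of the intervention: motivation, knowledge of what matters for effective communication, and ability. The Phase 3 Statistical analyses section reuses the Phase 2 control arm as a no-treatment control.

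**The concern.** The intervention consists of information and skills, so describing its content to a control participant delivers some of it. No stated rule prevents this before her T2. The request rule does not exclude control women or their support persons, and the disclosure rule depends on an event in the IG, not on the control participant's own measurement.

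The contrast in communication competences is at stake. If some controls gain part of the effect before T2, the control mean rises and the difference between arms probably narrows. The sample size states no allowance for this. The same control data return in Phase 3, so a comparison of the app group with the no-treatment arm would be affected too. The comparison in hypotheses 7 to 9, app against training without app, uses the other arm and is not touched by this route.

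**Working it through.** **Inputs from the protocol article (Phase 2 Procedure, power paragraph after Table 6):** d = 0.3, alpha 0.05, power 80%, 176 analysed per arm (352 in total).

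**Inputs not in the article, so assumed:** c, the share of control participants who receive content before T2; and r, the share of the full training effect that each of them gains.

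**1. Reproduce the stated figure.** The normal approximation gives n per arm = 2(1.960 + 0.842)² / 0.3² = 2 × 7.849 / 0.09 ≈ 174.4, so 175 per arm (350). The two-sided t-test gives 175.4, so 176 per arm (352), an exact match. A one-sided test would need only 138 per arm, so the stated number is two-sided. Power at 176 per arm is 80.1% (t-test) or 80.4% (normal).

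**2. Dilute the effect.** If the control mean rises by c × r × 0.30 standard deviations and the IG mean is unchanged, then d' = 0.30 × (1 − c × r).

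**3. Recompute power at 176 per arm.** Normal form: Φ(d' × √(176/2) − 1.960), with √88 = 9.381. For d' = 0.27 this is Φ(2.533 − 1.960) = Φ(0.573) ≈ 0.717.

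| c | r | c × r | d' | Power (t) | Power (normal) | Total N for 80% (normal) |
|---|---|---|---|---|---|---|
| 0 | – | 0 | 0.300 | 80.1% | 80.4% | 350 |
| 5% | 25% | 1.25% | 0.296 | 79.1% | 79.4% | 358 |
| 10% | 50% | 5% | 0.285 | 76.0% | 76.2% | 388 |
| 20% | 50% | 10% | 0.270 | 71.4% | 71.7% | 432 |
| 20% | 100% | 20% | 0.240 | 61.2% | 61.5% | 546 |

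Like the plan's own calculation, the table treats analysed participants as independent.

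**4. Read the time limit.** The phrase "can be performed after completion of the IG treatment to disclose the content of the intervention" can be taken in more than one way.

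- *An IG woman's own course, disclosure to her.* This sentence then gives control participants nothing directly. The request rule still covers them, without a limit.
- *All IG training at the site or in the trial.* Only controls not yet measured at that point are exposed.
- *Any IG course, disclosure to anyone.* Controls can be exposed through most of recruitment.

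The text does not choose between these, and none of them refers to T2.

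**The case against.** The strongest reply has four parts.

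*Unblinding is not disclosure.* Strictly, the request rule lets someone learn an allocation, and content is mentioned only with the completion limit. This is fair, and it is why the point is put as what may happen. But the trigger for unblinding is a request for information about the training, and the next two sentences provide for content and a flyer. No sentence excludes controls.

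*A flyer is not the training.* Patient training lasts about 8 hours and includes case exercises, self-efficacy work and action and coping plans. This stands. A flyer could plausibly carry the knowledge component but not the practice, so values of r near 100% are an upper bound.

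*This is a condensed article.* It does not say when T2 falls, and the fuller German protocol may hold operational detail. That limits any statement of how many controls are exposed. It does not answer the point, because the article itself states the rule and its time limit, and the limit is tied to the wrong event.

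*Staff already know the content.* A reader might infer that the flyer also leaks the intervention through ward staff. The documents do not support blaming this rule for that. In Phase 1, "The training will be offered to all professionals at both intervention sites", and for Phase 2 four "professionals will be taught in a train-the-trainer seminar" in each hospital. The flyer adds little by this route, so it is not part of the point.

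**Conclusion.** The point holds in a limited form. The published rule allows control participants to receive intervention content before T2, and its one time limit is undefined and unrelated to T2. Dilution of the Phase 2 contrast is the probable result. Its size cannot be derived from the article, which gives neither a request rate nor the flyer's content. Under the assumptions shown, the loss of power runs from negligible (about 79%) through moderate (71 to 72%), and reaches about 61% only if one control in five gains the whole effect.

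Some stronger conclusions are tempting but not supported:

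- *The measured effect will certainly shrink.* The outcome is a self-developed questionnaire, and people who learn their allocation may rate themselves differently in either direction.
- *The rule adds expectation effects in the IG.* Women who attend the training know that they were trained, whatever the rule says.
- *The rule distorts the planned analysis by motivation.* This would need evidence on who asks, and the article has none.

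**What to change.** Change the rule in the Phase 2 Procedure section as follows.

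1. Outside the assigned training, no participant receives the flyer or any description of training content until her own T2 and that of her support person are complete.
2. Define the completion point in the disclosure rule to match: for each participant and her support person, once both T2 measurements are in.
3. Answer earlier requests with a neutral statement that does not describe the training.
4. Log any earlier disclosure by date and arm, and use the log in a sensitivity analysis of the Phase 2 contrast and of any Phase 3 comparison with the no-treatment arm.

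The cost is one reworded rule and a short log. Sample size, allocation and use of the flyer after the study are unchanged. The small downside is that participants who ask must wait until T2 for the flyer.
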